**LABORATORY SCREENING FORM SP-FOLIC ACID IN PREGNANT WOMEN STUDY**

**(SPF-FORM 1b)**

***KEMRI/CDC***

**1.** Code SP [_].[_][_][_][_]

**2.** Date sample taken: [_][_]/[_][_]/[_][_][_][_]

**3.** Urine: Taken [_] 1=yes 2=no

Sulfa test [_] 1=positive 2=negative 9=unknown

**4.** Hb [_][_].[_] g/dl

**5.** Blood slide for malaria [_] 1=positive 2=negative 9=not done

If positive for malaria: count [_][_][_][_][_] / 300 WBC

Species: [_]

1 = plasmodium falciparum

2 = plasmodium falciparum and malariae

3 = plasmodium malariae

4 = plasmodium ovale

5=other, specify__________________________________

**6.** Unigold [_] 1=positive 2=negative 3=indeterminate 9=not done

1. Determine [_] 1=positive 2=negative 3=indeterminate 9=not done

**8.** Capillus [_] 1=positive 2=negative 3=indeterminate 9=not done

**9.** Sickle cell test [_] 1=sickle cell disease 2=sickle cell carrier

3= indeterminate status 4=No sickle cell carrier or disease

9=not done

**10.** Blood for folic acid taken [_] 1=yes 2=no

Place of storage in Kisian: _________________________________________________

**FOLLOW UP FORM** **SP-FOLIC ACID IN PREGNANT WOMEN STUDY (SPF-FORM 2)**

***KEMRI/CDC***

**1.** Code SP [_].[_][_][_][_]

1. Date [_][_]/[_][_]/[_][_][_][_]

Interviewer ____________________

1. Type of visit: [_] 1=Scheduled visit (day 2, 3, 7, 14, 21 and 28)

2=Visit to make up for a missed scheduled visit

3=Unscheduled visit (any other day)

Number of days past treatment with SP [_][_]

**4.** Did you use folic acid/placebo every day for the days between this visit and your last visit?

[_] 1 = yes 2=no

If no, how many days did you not take the tablets [_][_]

Did you bring your tablets folic acid (or placebo)? [_] 1=yes 2=no

If yes, number of tablets in the container [_][_]

**5.** Complaints: [_] 1=yes 2=no

If yes, specify

Axillary temperature: [_][_].[_] o C

**6.** Side-effects:

complaints of itching [_] 1=yes 2=no 9 = unknown

Complaints of rash [_] 1=yes 2=no 9 = unknown

Complaints of blisters [_] 1=yes 2=no 9 = unknown

Anything else [_] 1=yes 2=no 9 = unknown

If yes, specify

**If yes, on any of the above complaints: refer to the CO or study physician**

1. Did you use any medicine between your last and the present visit? [_] 1=yes 2=no

If yes, what medicine did you use, and for how long?

_________________________________________________________________________

**8.** Blood smear: Result: [_] 1=positive 2=negative 9=not done

If positive for malaria: count [_][_][_][_][_] / 300 WBC

Species: [_]

1 = plasmodium falciparum

2 = plasmodium falciparum and malariae

3 = plasmodium malariae

4 = plasmodium ovale

5=other, specify__________________________________

**9.** Blood for folate serum levels taken on day 7: [_] 1=yes 2=no 8 = not applicable

If yes, place of storage in Kisian: ____________________________________________

**10.** Hemoglobin (only on day 14 and 28 or on request): Hb [_][_].[_] g/dl

**11.**  Additional history and examination: (Examining clinical officer or physician ____________)

**12.**  Diagnosis (if complaints): **______________________________________________________**

**13.**  Medication given in study clinic, or other action taken: (if any)

**______________________________________________________________________________**

**14.** Conclusion: [_] 1) Continue, next appointment: [_][_]/[_][_]/[_][_]

2) Excluded: reason: [_]

3) Dropped out: reason:

4) End of study after 28 days

Reasons for exclusion:

1. Use of other sulfa containing drugs or antimalarials when being in the study.

2. RIII resistance: -A parasite density at Day 3 that is > 25% of the Day 0 parasite density.

3. RII resistance: -Parasites at 7 days and a positive blood smear at day 3 with a parasite density that is < 25% of the Day 0 parasite density.

4. Early RI: -A negative Day 3 blood smear with a positive blood smear on any day between Day 4 and Day 14 or a positive Day 3 blood smear with a parasite density that is < 25% of Day 0, a negative Day 7 blood smear, and a positive blood smear on any day between Day 8 and Day 14.

5. Sensitive or late RI: -A Day 3 parasite density that is <25% of the Day 0 density and negative blood smears on every follow-up examination between Day 7 and Day 14.

6. Other reason, specify_________________________________________________

**In case of clinical or parasitologic failure: treat with Quinine 600 mg TDS for 7 days, and make a new appointment after 7 days.**

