
***Definitions:***

Documented fever will be defined as an axillary temperature of 37.5 oC. Parasitaemia will be defined as the presence of any asexual bloodstage parasite of *Plasmodium falciparum* in a thick smear after inspection of microscopic fields until 300 leucocytes have been counted. A woman will be considered HIV-seropositive if both tests are positive and HIV-seronegative if both HIV-tests are negative. In case of an inconclusive result the rapid test Capillus HIV-1/HIV-2 (Cambridge Diagnostics, Wicklow, Ireland) will be used. Women with the hemoglobin phenotype HbAS will be defined as having sickle cell trait, and women with the hemoglobin phenotype HbSS will be defined as having sickle cell disease. Anemia will be defined as a hemoglobin < 11 g/dl, and severe anemia will be defined as a hemoglobin < 7 g/dl. For analysis a hemoglobin < 8 g/dl, moderate-to-severe anemia, will be considered because studies have indicated that a hemoglobin < 8 g/dl may be an important indicator in association with malaria (Verhoeff et al, 1998). Parasitologic failure and treatment failure will be used as previously described.

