Annex 2: Follow up schedule for participating pregnant women

| Day | Action | Form | Laboratory |
| --- | --- | --- | --- |
| 0 | a) Screening  b) Enrollment  c) Randomization  d) Supervised SP  e) Instruction and supply of folic acid/placebo tablets, supervised first dose  f) Supply of iron tablets 60 mg/day | Screening form  Enrollment form | Thin and thick blood smear  Hemoglobin  HIV-testing  Sickle cell test  Filter paper sample for PCR  Urine for sulfa test |
| 2 | a) Follow up,  b) Supervised folic acid/placebo | Follow up form | Thin and thick smear |
| 3 | a) Follow up  b) Supervised folic acid/placebo | Follow up form | Thin and thick smear |
| 7 | a) Follow up  b) Supervised folic acid/placebo | Follow up form | Thin and thick smear |
| 14 | a) Follow up  b) New supply folic acid tablets for all women | Follow up form | Thin and thick smear  Hemoglobin |
| 21 | a) Follow up  b) Supervised folic acid | Follow up form | Thin and thick smear  Filter paper sample for PCR |
| 28 | a) Follow up  b) New supply folic acid /iron | Follow up form | Thin and thick smear  Hemoglobin |
| x | Intercurrent visit: visit in between follow up visits | Follow up form | Thin and thick smear  Hemoglobin |

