**Late parasitological failure**:

- Presence of parasitemia on any day from day 7 to 28 and an axillary temperature of < 37.5 ºC without previously meeting any of the criteria of *Early Treatment Failure* or *Late Clinical Failure*

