**Interpretation of definition of treatment failure for the SP-folate staff (to be included in each participant file):**

**Visit result table**

| **Day** | **Day0** | **2** | **3** | **7** | **14** | **21** | **28** |  |
| --- | --- | --- | --- | --- | --- | --- | --- | --- |
| Blood smear result * |  |  |  |  |  |  |  |  |
| Axillary temperature** |  |  |  |  |  |  |  |  |
| Danger signs |  | Yes / No | Yes / No | Yes / No | Yes / No | Yes / No | Yes / No | Yes / No |
| Outcome |  | Continue / Stop | Continue / Stop | Continue  / Stop | Continue  / Stop | Continue  / Stop | Continue  / Stop | Continue  / Stop |

*Parasite density per 300 WBC **In degrees Celsius

**Danger signs** or signs of severe malaria in adults:

**Clinical**: Prostration (can’t sit up), Impaired consciousness (not responding to voice or pain stimulus), Respiratory distress (difficulty in breathing and fast breathing, Multiple convulsions (spasms of the muscles with jerky movements), Circulatory collapse (fainting), Pulmonary oedema (radiological), Abnormal bleeding (bleeding from nose, ears, mouth or any other body opening), Jaundice (yellow eyes), Haemoglobinuria (blood in urine)

**Laboratory**: Severe anemia (Hb < 7 g/dl), Hypoglycemia, Acidosis, Hyperlactataemia, Hyperparasitemia (parasite count ≥ 3750/300 WBC), Renal impairment

| **Day** | **Findings** | **What to do:** |
| --- | --- | --- |
| **1** | Parasitemia of 0 | Continue |
| **1** | Parasitemia < day 0, and no danger signs of severe malaria | Continue |
| **1** | Parasitemia (any density) and axillary temperature ≥ 37.5 ºC | Continue, give Paracetamol |
| **1** | **Danger signs in the presence of parasitemia** | **Treatment failure, exclude** |
| **2** | Parasitemia of 0 | Continue |
| **2** | Parasitemia < day 0, and no danger signs of severe malaria | Continue |
| **2** | Parasitemia < day 0, and an axillary temperature ≥ 37.5 ºC | Continue, give Paracetamol |
| **2** | **Parasitemia > day 0** | **Treatment failure, exclude** |
| **2** | **Danger signs in the presence of parasitemia** | **Treatment failure, exclude** |
| **3** | Parasitemia of 0 | Continue |
| **3** | Parasitemia < 25% of day 0, and no danger signs, and an axillary temperature < 37.5 ºC | Continue |
| **3** | **Parasitemia < 25% of day 0, and an axillary temperature ≥ 37.5 ºC** | **Treatment failure, exclude** |
| **3** | **Parasitemia ≥ 25% of day 0 count** | **Treatment failure, exclude** |

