| **3** | **Danger signs in the presence of parasitemia** | **Treatment failure, exclude** |
| **4-6** | Parasitemia of 0 | Continue |
| **4-6** | Parasitemia and no danger signs and an axillary temperature < 37.5 ºC | Continue |
| **4-6** | **Parasitemia > 0 and an axillary temperature ≥ 37.5 ºC** | **Treatment failure, exclude** |
| **4-6** | **Danger signs in the presence of parasitemia** | **Treatment failure, exclude** |
| **7-28** | Parasitemia of 0 | Continue |
| **7-28** | **Any parasitemia**  **(either or not danger signs or an axillary temperature ≥ 37.5 ºC)** | **Treatment failure, exclude** |

**If treatment failure, treat with Quinine.** Make a check appointment for after one week.

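### Follow-up form item 14 codes exclusions with a 14-day RI–RIII scheme that contradicts the 28-day failure definitions, most directly for an afebrile positive smear on days 4–6

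*Protocol*

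**What the plan says.** **Failure definitions.** Section VII.D and Annex 5 define early treatment failure (days 1–3), late clinical failure (after day 3, with fever or danger signs) and late parasitological failure, the last as "Presence of parasitemia on any day from day 7 to 28" without fever. The staff table in Annex 5 turns these into day-by-day instructions and goes into every participant's file. Its days 4–6 row for "Parasitemia and no danger signs and an axillary temperature < 37.5 ºC" gives the instruction to continue. From day 7 any parasitaemia is a failure.

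**The follow up form.** Item 14 offers four conclusions: continue, excluded with a reason, dropped out, or end of study at 28 days. The printed reasons for exclusion are use of other antimalarial or sulfa drugs (1), RIII (2), RII (3), Early RI (4), *Sensitive or late RI* (5) and other (6). The first limb of reason 4 is "A negative Day 3 blood smear with a positive blood smear on any day between Day 4 and Day 14". A date is entered only beside the option "Continue, next appointment".

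**When a day 4–6 smear can occur.** Scheduled visits fall on days 2, 3, 7, 14, 21 and 28. Annex 2 adds a row for an "Intercurrent visit: visit in between follow up visits", with the same form and a smear, and the form has a code for unscheduled visits.

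**The concern.** Staff complete both documents for the same woman at the same visit. If they disagree on whether she stays in the study, follow-up depends on which one the clinician reads. The trial is sized on parasitological failure at day 7, and haemoglobin change is measured to day 28. A woman excluded on day 5 has no next appointment on the form, so both assessments may be lost. Under Annex 5 she would be seen on day 7, counted as a failure if still positive, and continued if clear.

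The rest of the list raises the same doubt. Its windows stop at day 14 and its categories are not those of the 28-day definitions, so the recorded exclusion code cannot be relied on to say why a woman left.

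**Working it through.** The plan states no figure on this point, so the check sets the two rule sets side by side. Cases are afebrile and without danger signs unless stated.

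| Day 3 smear | Later course | Form item 14 | Annex 5 |
|---|---|---|---|
| Negative | Positive on day 4, 5 or 6 | Reason 4 | Continue |
| Negative | First positive on days 7–14 | Reason 4 | Late parasitological failure |
| Positive, < 25% of day 0 | Positive on days 4–6 | No reason met | Continue |
| Positive, < 25% | Positive on day 7 | Reason 3 | Late parasitological failure |
| Positive, < 25% | Day 7 negative, positive on days 8–14 | Reason 4 | Late parasitological failure |
| Negative or < 25% | First positive after day 3 on day 21 or 28 | Reason 5 or 6 | Late parasitological failure |
| Negative or < 25% | Smear-negative from day 7 onward | Reason 5 | Continue to day 28 |
| Exactly 25% | Any | No specific reason | Early treatment failure |
| > 25% | Any | Reason 2 | Early treatment failure |

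1. **Days 4–6.** The first row is a direct conflict between excluding and continuing. It requires a negative day-3 smear, an unscheduled visit on days 4–6, a positive smear, no fever and no danger signs. A late make-up smear for a missed day 3 does not meet reason 4, because that reason needs a negative day-3 result. From day 7 both rules remove the woman.

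2. **Reason 5.** Taken literally, it lists the women in whom treatment worked. The same form has day 21 and day 28 visits and an end-of-study option at 28 days, so it cannot be meant as an exclusion. It suggests that a classification table was placed under the wrong heading.

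3. **Day-3 threshold.** Reason 2 needs more than 25% and reasons 3 to 5 need less than 25% (or a negative smear). Annex 5 counts 25% or more as early failure. A count of exactly 25% therefore has no specific code.

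4. **Other gaps.** Three early-failure criteria have no reason of their own: danger signs, a day-2 count above day 0, and day-3 parasitaemia below 25% with fever. These affect the code only. Smear counts, temperature and days since SP are on the form, and danger signs are in the Annex 5 visit table, so the outcome can be derived.

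**The case against.** The strongest reply is that the list only supplies codes once exclusion has been decided and does not order anyone's removal. If reason 5 cannot be operative, reason 4 beside it is weak evidence that staff would remove a woman on day 5. Section VII.D, the quinine rule under Follow up in VII.E and the Annex 5 staff table all agree that an afebrile day 4–6 positive is not a failure. The Data analysis section compares cumulative parasite failure by arm and uses neither RI–RIII grades nor item 14 codes.

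Most of this stands. The intended rule is clear, and the defect lies in the form rather than in the analysis. But the list is headed as reasons for exclusion, it is what staff enter at item 14, and nothing says that Annex 5 overrides it.

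Rarity also stands. Women are told to return for fever or complaints, and a febrile positive on days 4–6 is late clinical failure under Annex 5, with no conflict over removal.

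Three stronger readings are tempting, and the documents do not support them:

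- *The form orders quinine on days 4–6.* Its quinine line applies to clinical or parasitologic failure. The Definitions paragraph in VII.E says "Parasitologic failure and treatment failure will be used as previously described", and that earlier description starts parasitological failure at day 7.
- *The conflict lowers the day-7 failure rate by a stated amount.* The protocol does not say how a woman excluded on day 5 is counted. She might be set to missing, or counted as a success or a failure, so neither direction nor size follows.
- *Failures at days 21 and 28 go unrecorded.* The smear is recorded in either case. At day 28 the end-of-study option is available and no scheduled follow-up visit remains to lose.

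**Conclusion.** The point holds and is minor. Item 14 contradicts the protocol's own failure definitions. The conflict that can change follow-up is reason 4 for an afebrile positive smear on days 4–6 after a negative day 3. The misplaced reason 5, the 25% boundary and the missing categories make the exclusion code unreliable but do not remove an endpoint.

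No frequency of such visits is given and none is assumed, so no effect on the day-7 comparison can be stated. Confidence is high for the mismatch in the text. That a woman would actually lose her day-7 smear is only a possibility: it assumes that staff follow the form's list rather than the Annex 5 table.

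**What to change.** On the follow up form, replace reasons 2–5 with the Annex 5 categories: early treatment failure (including a day-3 count of 25% or more of day 0), late clinical failure, and late parasitological failure from day 7. This removes *Sensitive or late RI* as a reason for exclusion. Add a line that the Annex 5 staff table governs, so that an afebrile woman without danger signs who is positive on days 4–6 continues to her day-7 smear.

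The cost is one list on one form and a short staff briefing. Completed forms can be recoded from the recorded counts, temperatures, days since SP and danger signs, and RI–RIII grades can still be derived if wanted. A woman already excluded on days 4–6 without a day-7 smear cannot be recovered. The change adds no clinical delay beyond what Annex 5 already accepts.

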**For women severely ill, arrange admission in the Provincial Hospital**

**Annex 5: Definition of treatment failure SP-Folate study**

**Early treatment failure**:

- Development of **danger signs** or severe malaria on day 1, day 2, or day 3, in the presence of parasitemia.

**Danger signs** or signs of severe malaria in adults:

Clinical:

- - - Prostration (can’t sit up)
    - Impaired consciousness (not responding to voice or pain stimulus)
    - Respiratory distress (difficulty in breathing and fast breathing
    - Multiple convulsions (spasms of the muscles with jerky movements)
    - Circulatory collapse (fainting)
    - Pulmonary oedema (radiological)
    - Abnormal bleeding (bleeding from nose, ears, mouth or any other body opening)
    - Jaundice (yellow eyes)
    - Haemoglobinuria (blood in urine)

Laboratory:

- - - Severe anemia (Hb < 7 g/dl)
    - Hypoglycemia
    - Acidosis
    - Hyperlactataemia
    - Hyperparasitemia
    - Renal impairment
- Parasitemia on day 2 higher than day 0 count, irrespective of axillary temperature
- Parasitemia on day 3 with an axillary temperature ≥ 37.5
- Parasitemia on day 3 ≥ 25% of count on day 0

**Late clinical failure**:

- Development of danger signs of severe malaria after day 3 in the presence of parasitemia without previously meeting any of the criteria of *Early Treatment Failure*
- Presence of parasitemia and an axillary temperature ≥ 37.5 ºC on any day from day 4 to 28 without previously meeting any of the criteria of *Early Treatment Failure*

**Late parasitological failure**:

- Presence of parasitemia on any day from day 7 to 28 and an axillary temperature of < 37.5 ºC without previously meeting any of the criteria of *Early Treatment Failure* or *Late Clinical Failure*

**Interpretation of definition of treatment failure for the SP-folate staff (to be included in each participant file):**

**Visit result table**

| **Day** | **Day0** | **2** | **3** | **7** | **14** | **21** | **28** |  |
| --- | --- | --- | --- | --- | --- | --- | --- | --- |
| Blood smear result * |  |  |  |  |  |  |  |  |
| Axillary temperature** |  |  |  |  |  |  |  |  |
| Danger signs |  | Yes / No | Yes / No | Yes / No | Yes / No | Yes / No | Yes / No | Yes / No |
| Outcome |  | Continue / Stop | Continue / Stop | Continue  / Stop | Continue  / Stop | Continue  / Stop | Continue  / Stop | Continue  / Stop |

*Parasite density per 300 WBC **In degrees Celsius

**Danger signs** or signs of severe malaria in adults:

**Clinical**: Prostration (can’t sit up), Impaired consciousness (not responding to voice or pain stimulus), Respiratory distress (difficulty in breathing and fast breathing, Multiple convulsions (spasms of the muscles with jerky movements), Circulatory collapse (fainting), Pulmonary oedema (radiological), Abnormal bleeding (bleeding from nose, ears, mouth or any other body opening), Jaundice (yellow eyes), Haemoglobinuria (blood in urine)

**Laboratory**: Severe anemia (Hb < 7 g/dl), Hypoglycemia, Acidosis, Hyperlactataemia, Hyperparasitemia (parasite count ≥ 3750/300 WBC), Renal impairment

| **Day** | **Findings** | **What to do:** |
| --- | --- | --- |
| **1** | Parasitemia of 0 | Continue |
| **1** | Parasitemia < day 0, and no danger signs of severe malaria | Continue |
| **1** | Parasitemia (any density) and axillary temperature ≥ 37.5 ºC | Continue, give Paracetamol |
| **1** | **Danger signs in the presence of parasitemia** | **Treatment failure, exclude** |
| **2** | Parasitemia of 0 | Continue |
| **2** | Parasitemia < day 0, and no danger signs of severe malaria | Continue |
| **2** | Parasitemia < day 0, and an axillary temperature ≥ 37.5 ºC | Continue, give Paracetamol |
| **2** | **Parasitemia > day 0** | **Treatment failure, exclude** |
| **2** | **Danger signs in the presence of parasitemia** | **Treatment failure, exclude** |
| **3** | Parasitemia of 0 | Continue |
| **3** | Parasitemia < 25% of day 0, and no danger signs, and an axillary temperature < 37.5 ºC | Continue |
| **3** | **Parasitemia < 25% of day 0, and an axillary temperature ≥ 37.5 ºC** | **Treatment failure, exclude** |
| **3** | **Parasitemia ≥ 25% of day 0 count** | **Treatment failure, exclude** |
| **3** | **Danger signs in the presence of parasitemia** | **Treatment failure, exclude** |
| **4-6** | Parasitemia of 0 | Continue |
| **4-6** | Parasitemia and no danger signs and an axillary temperature < 37.5 ºC | Continue |
| **4-6** | **Parasitemia > 0 and an axillary temperature ≥ 37.5 ºC** | **Treatment failure, exclude** |
| **4-6** | **Danger signs in the presence of parasitemia** | **Treatment failure, exclude** |
| **7-28** | Parasitemia of 0 | Continue |
| **7-28** | **Any parasitemia**  **(either or not danger signs or an axillary temperature ≥ 37.5 ºC)** | **Treatment failure, exclude** |

**If treatment failure, treat with Quinine.** Make a check appointment for after one week.
